**Funder**

TBA

This protocol describes the CHIP study and provides information about procedures for entering participants. Every care was taken in its drafting, but corrections or amendments may be necessary. These will be circulated to investigators in the study.

Problems relating to this study should be referred, in the first instance, to the Chief Investigator.

This study will adhere to the principles outlined in the UK Policy Framework for Health and Social Care Research ver. 3.0 (2017). It will be conducted in compliance with the protocol, the Data Protection Act and other regulatory requirements as appropriate.

**Glossary of Abbreviations and technical terms**

|  |  |
| --- | --- |
| RT-PCR | Real-time reverse transcriptase-polymerase chain reaction |
| PPE | Personal protective equipment |
| BAME | Black and minority ethnic groups |
| NIHR | National institute of healthcare research |
| ONS | Office of National Statistics |
| UKRI | UK research and innovation |
| SARS-CoV-2 | Severe acute respiratory syndrome coronavirus 2 |
| IMD | Index of multiple deprivation |
| RWT | The Royal Wolverhampton NHS Trust |
| SMS | Short message service (text message) |
| R&D | Research & Development |
| SOP | Standard Operating Procedure |
| HR | Human Resources |
|  |  |
|  |  |
|  |  |
|  |  |
|  |  |
|  |  |
|  |  |
|  |  |
|  |  |
|  |  |
|  |  |
|  |  |
|  |  |
|  |  |
|  |  |
|  |  |
|  |  |
|  |  |

**Keywords**

Coronavirus

COVID-19

Antibody

Test

**Study Summary**

| **TITLE** | A pilot assessment of the COVID 19 antibody status and associated factors, in individuals employed by a large acute NHS trust during the Coronavirus pandemic  **SHORT STUDY TITLE / ACRONYM:**  COVID-19 health professional impact study (**CHIP**) |
| --- | --- |
| **DESIGN** | Observational retrospective analysis. |
| **AIMS** | To determine the factors associated with antibody positivity in employees of a large NHS trust having passed through the first peak of the COVID-19 pandemic |
| **OUTCOME MEASURES** | Proportion of antibody positive participants, associations with workplace, work type, demographics and behavioural factors, ethnicity, and symptoms |
| **POPULATION** | NHS Trust employees self referring for routine COVID -19 antibody testing |
| **ELIGIBILITY** | All employees tested for Coronavirus antibodies |
| **duration** | 1 year 3 months  Recruitment period of 3 months with participation duration of 1 year. |

# 1. INTRODUCTION

## BACKGROUND

The COVID-19 pandemic has had a huge impact on healthcare resources and staff in the UK. Understanding the key risk factors associated with infection amongst healthcare workers is essential for future pandemic response plans. Currently there are scarce data relating to the infection rates and associated factors amongst healthcare workers in the UK.

Whilst many of the healthcare challenges posed by the current pandemic have centred around a shortage of physical resources (access to ventilators, hospital beds, PPE availability), these are being remedied with improvements in manufacture and supply. However, Human Resources are less easy to replace and the impact of COVID -19 has been disproportionately high on healthcare workers, with a documented 106 individuals dying in the UK in April 2020 alone.

Studies of infection rates in healthcare workers have largely relied on the real-time reverse transcriptase-polymerase chain reaction (RT-PCR) test to date.

One study of 50% of staff at the privately run Portland hospital showed that at the height of the pandemic, 18% of staff tested positive, with a higher degree of positive results in patient-facing staff^1^.. Interestingly they showed that staff living in more socially deprived areas were significantly more likely to test positive for the virus.

Healthcare workers are twice as likely to succumb to Coronavirus infection, when compared to the general population and those from Black and minority ethnic (BAME) backgrounds appear to be particularly at risk (ONS statistics).

In contrast, the COVIDSORTIUM study, conducted at a large London teaching hospital reported a peak infection rate amongst staff of 7.1% falling rapidly over following weeks to approximately 1% suggesting that infection amongst health workers reflected that of the general population^2^.

UK research and innovation (UKRI) and National institute of healthcare research (NIHR) have recently put out a call for research into the risk factors, transmission and prevalence of severe acute respiratory syndrome coronavirus 2 (SARS-CoV-2).

Currently there is no evidence that the presence of SARS-CoV-2 antibodies provides long term immunity to future infection. In this study we will follow subjects at six months and one year to determine new infection rates in those with antibodies and those without at the time of initial testing.

In this project we aim to describe the prevalence of SARS-CoV-2 antibody presence in an acute NHS hospital that was particularly hard hit by the first wave of the pandemic and relate prevalence rate amongst staff to:

- Patient Facing vs Non Patient facing
- Previous RT-PCR test
- Previous RT-PCR test positive
- Symptomatic in past vs asymptomatic
- Types of symptoms reported
- Time lapse between reported symptoms and SARS-CoV-2 antibody test
- Age
- Ethnicity
- Index of multiple deprivation (IMD) from Postcode
- Previous period of self isolation or not
- Degree of anxiety regarding infection with virus
- Presence of one or more high risk factors for COVID 19

In addition we will relate the presence or absence of SARS-CoV-2 antibody at the time of testing to the future incidence of clinical COVID-19 infection^3^. The significance of antibody presence and if it confers protection to future sars-Cov2 infection is unknown.

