# 2. STUDY OBJECTIVES

To determine:

1. The prevalence of SARS-CoV-2 antibody positivity in healthcare staff in an acute NHS trust that has passed through the first peak of Coronavirus infection
2. To assess the relative importance of
   1. Job role
   2. Age
   3. Ethnicity
   4. Previous RT-PCR test status
   5. Previous clinical infection
   6. Index of multiple deprivation
   7. Previous period of self isolation
   8. Level of anxiety regarding COVID 19
   9. Presence of one or more high risk factors for COVID 19
   10. Presence or absence of self-reported previous COVID 19 symptoms
3. To assess whether antibody positivity reduces risk of clinical SARS-CoV-2 infection in the following 12 months.

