# 3. STUDY DESIGN

This observational study will utilise the results of the Abbott SARS-CoV-2 IgG assay analysed on either Abbott Architect i2000sr or Alinity ci (Abbott Diagnostics, Abbott Park, IL, USA) and in addition consent will be gained to retrieve and analyse data held by the Trust in relation to this test.

Subjects will be invited to take part, by SMS, via the HR department, in a smart - phone based questionnaire to gain additional data as detailed above.

All employees of the Royal Wolverhampton Trust (RWT) requesting an antibody test for SARS-CoV-2 will be approached to be part of the study – it is estimated that this will be up to 4000 individuals and we aim for a response from 3000 participants.

The study will also be advertised via trust communication methods – the screen saver, the weekly bullet-in, email to all through comms. This will act as a reminder for staff who have had the antibody testing to complete the questionnaire via the SMS link, but also offer an alternative method to access the online PIS, consent and complete the questionnaire if they did not provide a mobile telephone number for the SMS main recruitment method.

Consent for inclusion to the study will be gained by the smartphone link that will then lead on to the questionnaire (survey monkey). If they have not provided a mobile number to enable SMS, alternative method of contact such as email or letter will be used.

If after sending the SMS the questionnaire has not been completed after 2 weeks, a reminder SMS will be sent out.

A further follow up questionnaire will be sent at six and twelve months to determine clinical COVID status by SMS (or alternative method if mobile number not provided).

Data will be collected, linked, de-identified and stored on a dedicated database, on RWT trust servers. Data processing will be performed by a dedicated clinical trial assistant (CTA). Study data will only be accessible by the CTA, study manager or chief investigators. The data will be retrieved, and pseudoanonymised data will be analysed by the investigators and study statistician.

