## 3.1 Study outcome measures

Primary Outcome:

- To identify the proportion of employees tested who have evidence of SARS-CoV-2 antibodies
- To identify factors associated with a positive test
  - Type of healthcare role
  - Ethnicity
  - Age
  - Index of multiple deprivation
  - Previous RT-PCR test status
  - Previous clinical COVID infection
  - Previous period of self isolation
  - Level of COVID-19 related anxiety
  - Presence of one or more high risk factors for COVID 19
  - Presence or absence of self-reported COVID 19 symptoms
- To assess the likelihood of clinically relevant (causing illness) infection with SARS-CoV-2in subjects with both positive and negative SARS-CoV-2 antibody tests.

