## 4.1 Inclusion Criteria

- All Staff employed by RWT, having undergone the SARS-CoV-2antibody test at the Trust’s testing facility will be eligible for inclusion in the study irrespective of antibody status.

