**Study Schedule:**

| **Procedures** |  |  |  |  |
| --- | --- | --- | --- | --- |
|  | **Screening** | **Baseline** | **6 Months** | **12 Months** |
| Consent for SMS link | X |  |  |  |
| Informed consent (online) |  | X |  |  |
| Initial questionnaire |  | X |  |  |
| Linkage to HR data |  | X |  |  |
| Linkage to antibody test |  | X |  |  |
| Questionnaire - follow up |  |  | X | X |

The study will end when all RWT employees have had the antibody test and been contacted to be part of the study or 3,000 subjects are recruited, whichever is sooner.

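### Objective 3 has no lead-in after the antibody test and no stated dating of episodes, so infections already under way can count as later infections, mainly in the antibody-negative group

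*Protocol*

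**What the plan says.** Section 3.1 of the protocol lists as an outcome "To assess the likelihood of clinically relevant (causing illness) infection with SARS-CoV-2in subjects with both positive and negative SARS-CoV-2 antibody tests". Objective 3 in section 2 asks whether antibody positivity lowers the risk of clinical infection over the next 12 months. The Background says that the groups are formed by antibody presence or absence at the initial test.

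On the test, section 3 states "This observational study will utilise the results of the Abbott SARS-CoV-2 IgG assay". The Study Schedule links the antibody result at baseline only. Staff refer themselves for testing, and section 4.1 makes anyone tested eligible ("will be eligible for inclusion in the study irrespective of antibody status"), with no condition on the interval since symptoms.

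On the outcome, sections 3 and 5 send questionnaires at 6 and 12 months. The data-collection part of section 5 says that one questionnaire serves all time-points. It lists symptom details without saying that onset dates are recorded.

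On timing, the aims list in the Background includes "Time lapse between reported symptoms and SARS-CoV-2 antibody test". The corresponding item in section 2 is "Presence or absence of self-reported previous COVID 19 symptoms", and in section 3.1 it is "Presence or absence of self-reported COVID 19 symptoms". Neither list contains the time lapse.

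**The concern.** IgG appears some time after infection. A person who is incubating, or in the early phase of illness, can be infected and still test IgG-negative. If that illness is later reported on a follow-up questionnaire, nothing in the protocol separates it from an infection acquired after the test. It then counts as an event in the antibody-negative group.

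Such events fall mainly on one side of the comparison. They raise the negative group's risk and push the risk ratio (positive over negative) below its true value, so antibodies look more protective than they are. The protocol itself says that it is unknown whether antibodies protect, so this is the comparison in which a directional artefact matters most.

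A smaller, separate issue affects the factor analysis. Recently infected staff may sit among the negatives, and the variable that would partly show this, time from symptoms to test, is missing from the formal objectives and outcomes.

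**Working it through.** **The plan's own figure.** Section 6 expects a 16% positive rate in 3,000 tests: 3,000 x 0.16 = 480 positives. This reproduces exactly and leaves 3,000 - 480 = 2,520 negatives. There is no power calculation to reproduce.

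**Early events with no true protection.** Let r be the 12-month risk of a new clinical infection, the same in both groups. Let e be the share of IgG-negatives whose infection was already under way at the test and who are counted as later cases. The protocol gives neither value; both are assumptions. If no such events occur among positives:

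observed risk ratio = r / (r + e)

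| r | e | Observed risk ratio (true value 1) |
|---|---|---|
| 5% | 1% | 0.05 / 0.06 = 0.83 |
| 3% | 1% | 0.03 / 0.04 = 0.75 |
| 5% | 0.5% | 0.05 / 0.055 = 0.91 |
| 3% | 0.5% | 0.03 / 0.035 = 0.86 |

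In the first row, 2,520 x 0.05 = 126 true events among negatives are joined by 2,520 x 0.01, about 25, giving 151. Positives have 480 x 0.05 = 24.

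**Relaxing the one-sided assumption.** If positives carry a fraction k of the same contamination, because some re-report an episode that was continuing at the test:

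observed risk ratio = (r + k e) / (r + e)

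With r = 5%, e = 1% and k = 0.5 (an assumption), this is 0.055 / 0.060 = 0.92. Alternatively, if the baseline questionnaire captured half of the early illness, e would fall from 1% to 0.5%, and 0.83 would become 0.91.

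**Against sampling error.** For 24/480 against 151/2,520, the standard error of the log risk ratio is sqrt(1/24 - 1/480 + 1/151 - 1/2,520) = 0.214. The approximate 95% interval around 0.83 is 0.55 to 1.27, so the bias lies inside sampling error.

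**The opposite mechanism.** Past infections that tested negative would dilute true protection. Suppose a share f of previously infected staff test negative, and these people carry the same later risk as positives. Then s = 3,000 x (0.16/(1 - f) - 0.16) / 2,520 is their share of the negative group, and the observed ratio is RR / ((1 - s) + s RR). With f = 30% (an assumption), s = 206 / 2,520 = 8.2%, and a true ratio of 0.20 appears as 0.214. This moves towards 1 and is small. It does not describe early events, which act in the other direction.

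**The case against.** Several points on the other side are sound.

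- **The time lapse is not abandoned.** A reader might infer that it is, but the Background still states it as an aim, section 1.2 points back to that list, and symptom details are collected. The types of symptoms reported are likewise in the Background list and absent later, so sections 2 and 3.1 look condensed. This is a mismatch of text.
- **The IgG result is not generally used as infection status.** Only the rationale in section 1.2 infers infection risk from it. Objectives 1 and 3 concern antibody positivity, and for seroprevalence an IgG-negative person is correctly classified whatever the interval. Previous RT-PCR status and previous clinical infection also remain in the objectives and outcomes.
- **The events are not confined to negatives.** A positive person still ill around the test could report that episode at follow-up.
- **Some early illness may be caught at baseline.** Invitation, consent and the first questionnaire come after the test, and that questionnaire covers symptoms. The protocol does not fix a start date for follow-up in either direction.
- **The assumed 1% is probably near a ceiling.** The nearest figure in the protocol is the roughly 1% staff infection rate at another hospital after its peak. That counts all infected staff, while e needs people who were IgG-negative, became ill, and were counted at follow-up.
- **An event window could sit in the statistical analysis plan,** which is not shown.

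The last point only goes so far. If onset dates are not collected, no later analysis plan can apply a window or carry out the time-lapse aim reliably. What to record on the questionnaire is a protocol decision.

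**Conclusion.** The point stands as a cheap improvement to objective 3. Antibody groups are fixed by one test, outcomes come from the same questionnaire at each time-point, and no stated rule separates an infection under way at the test from a new one. The resulting bias favours apparent protection.

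Its size cannot be derived from the protocol. For assumed values of 0.5-1% contamination and 3-5% risk, a true ratio of 1 would appear as 0.75-0.91. Re-reporting by positives or capture at baseline brings it closer to 1. Testing after the first peak makes a small effect the likelier case.

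A reader might go further and infer that any protective association from this study would be an artefact. The documents do not support that: they give no seroconversion time, test sensitivity or infection rate for this Trust at the time of testing. Nor would adding the time lapse to sections 2 and 3.1 remove the objective 3 bias, because someone incubating at the test has no earlier symptom onset to report.

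**What to change.** 1. State in section 5 that symptom-onset dates are recorded at baseline and at each follow-up, and that the test date is held in the linked dataset. This needs settling before the baseline questionnaire goes out, because dates recalled later are less reliable.
2. For objective 3, count only episodes with onset after a pre-specified lead-in from the test date, in both antibody groups, and report earlier episodes separately. Fourteen days is one example. The protocol contains no basis for a particular interval, so the sponsor should justify the choice.
3. Add the time from symptoms to test to the lists in sections 2 and 3.1, to match the Background.
4. Add a sensitivity analysis of the factor associations that excludes participants with symptom onset shortly before the test. State that it cannot identify people who were asymptomatic or incubating at the test.

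The cost is a few sentences, date fields on the questionnaire and one extra analysis. Some early events leave the objective 3 comparison. With a 14-day lead-in, 5% risk and events spread evenly over the year (all assumptions), that is 126 x 14/365, about 5 true events among negatives, and 24 x 14/365, about 1 among positives.

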**1.2 RATIONALE FOR CURRENT STUDY**

The current study aims to detail the current level of SARS-CoV-2 antibody positivity and thereby infer the likely risk to healthcare workers in the UK to COVID-19 infection^3^. We will determine whether certain characteristics (detailed above) will have an impact on likelihood of infection and antibody response. Furthermore we will determine the impact of the presence of antibodies on the likelihood of future clinical infection over a 12 month period.

# 2. STUDY OBJECTIVES

To determine:

1. The prevalence of SARS-CoV-2 antibody positivity in healthcare staff in an acute NHS trust that has passed through the first peak of Coronavirus infection
2. To assess the relative importance of
   1. Job role
   2. Age
   3. Ethnicity
   4. Previous RT-PCR test status
   5. Previous clinical infection
   6. Index of multiple deprivation
   7. Previous period of self isolation
   8. Level of anxiety regarding COVID 19
   9. Presence of one or more high risk factors for COVID 19
   10. Presence or absence of self-reported previous COVID 19 symptoms
3. To assess whether antibody positivity reduces risk of clinical SARS-CoV-2 infection in the following 12 months.

# 3. STUDY DESIGN

This observational study will utilise the results of the Abbott SARS-CoV-2 IgG assay analysed on either Abbott Architect i2000sr or Alinity ci (Abbott Diagnostics, Abbott Park, IL, USA) and in addition consent will be gained to retrieve and analyse data held by the Trust in relation to this test.

Subjects will be invited to take part, by SMS, via the HR department, in a smart - phone based questionnaire to gain additional data as detailed above.

All employees of the Royal Wolverhampton Trust (RWT) requesting an antibody test for SARS-CoV-2 will be approached to be part of the study – it is estimated that this will be up to 4000 individuals and we aim for a response from 3000 participants.

The study will also be advertised via trust communication methods – the screen saver, the weekly bullet-in, email to all through comms. This will act as a reminder for staff who have had the antibody testing to complete the questionnaire via the SMS link, but also offer an alternative method to access the online PIS, consent and complete the questionnaire if they did not provide a mobile telephone number for the SMS main recruitment method.

Consent for inclusion to the study will be gained by the smartphone link that will then lead on to the questionnaire (survey monkey). If they have not provided a mobile number to enable SMS, alternative method of contact such as email or letter will be used.

If after sending the SMS the questionnaire has not been completed after 2 weeks, a reminder SMS will be sent out.

A further follow up questionnaire will be sent at six and twelve months to determine clinical COVID status by SMS (or alternative method if mobile number not provided).

Data will be collected, linked, de-identified and stored on a dedicated database, on RWT trust servers. Data processing will be performed by a dedicated clinical trial assistant (CTA). Study data will only be accessible by the CTA, study manager or chief investigators. The data will be retrieved, and pseudoanonymised data will be analysed by the investigators and study statistician.

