**Data Collection – Questionnaire:**

Data to be collected from the questionnaire includes:

- Demographics such as Ethnicity, Age Group, Occupation, notification of patient-facing role
- Symptomatic details
- High-risk classification
- Wellbeing status through elements of the validated SF12 and the GAD7 questionnaires

The same questionnaire will be used at all time-points.

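### Whether antibodies reduce later infection rests on self-report questionnaires alone, because Trust-record linkage is scheduled only at baseline

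*Protocol*

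**What the plan says.** Protocol section 2 sets the third objective: "To assess whether antibody positivity reduces risk of clinical SARS-CoV-2 infection in the following 12 months". Section 3.1 lists the matching measure under Primary Outcome: "To assess the likelihood of clinically relevant (causing illness) infection".

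Section 3 gives the means of finding these infections: "A further follow up questionnaire will be sent at six and twelve months to determine clinical COVID status by SMS", or by another method where no mobile number was given. Section 5 adds one reminder after two weeks and, under Data Collection, says: "The same questionnaire will be used at all time-points".

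In the Study Schedule, the rows "Linkage to HR data" and linkage to the antibody test are each marked at Baseline and left empty at 6 and 12 months. The follow-up questionnaire is the only procedure in those two columns. Section 5 describes the linked data as the antibody result plus the details given at testing (identifiers, date of birth, address, postcode, mobile number).

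On consent, section 3 says "consent will be gained to retrieve and analyse data held by the Trust in relation to this test". Sections 7.1 and 7.2 go further and include data held by HR, without defining them.

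**The concern.** The comparison in objective 3 is between antibody-positive and antibody-negative staff, and the outcome is what those same people report. The Protocol does not say that participants are told their result. It is a strong inference: staff refer themselves for a routine test, section 5 has them sign that they understand its implications, section 7.1 says results are available, and nothing provides for masking. A person who believes they are immune may be less ready to call an illness COVID-19, and a person who believes they are not immune may be more ready. The reverse is also possible.

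Separately, the outcome exists only for those who answer. A participant who has died, or who is too ill at both contact points, cannot enter it by any other route.

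At stake is whether a difference, or the lack of one, can be read as a statement about protection rather than about who reports and who replies.

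**Working it through.** **The plan's own figure.** Section 6: 3,000 × 0.16 = 480 antibody-positive participants, which reproduces and leaves 2,520 negative. The Protocol gives no expected incidence, reporting accuracy or follow-up response. All such rates below are assumptions chosen to show scale.

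**1. Differential reporting, no true effect.** Observed risk = incidence × proportion of episodes reported + (1 − incidence) × false-report rate. Incidence is 5% in both groups (true RR 1.0).

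- Positives, 70% reported and 1% false: 0.05 × 0.70 + 0.95 × 0.01 = 0.0445.
- Positives, 80% and 2%: 0.05 × 0.80 + 0.95 × 0.02 = 0.0590.
- Negatives, 90% and 3%: 0.05 × 0.90 + 0.95 × 0.03 = 0.0735.
- Negatives, 90% and 5%: 0.05 × 0.90 + 0.95 × 0.05 = 0.0925.

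The extremes are 0.0445/0.0925 = 0.48 and 0.0590/0.0735 = 0.80. Apparent protection of 20% to 52% arises with none present.

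**2. Differential reporting, true protection.** True RR is 0.50, with 5% incidence in negatives and 2.5% in positives. Both groups report 90% of episodes; false reports are 3% in positives and 1% in negatives.

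- Positives: 0.025 × 0.90 + 0.975 × 0.03 = 0.0518.
- Negatives: 0.05 × 0.90 + 0.95 × 0.01 = 0.0545.

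Observed RR is 0.95, so real protection is nearly hidden. The direction of bias cannot be fixed from the Protocol.

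**3. Non-response related to illness only.** Observed risk = r·q₁ / (r·q₁ + (1 − r)·q₀), where r is the true risk and q₁ and q₀ are the response rates of infected and uninfected participants. With q₁ = 50% and q₀ = 70% in both antibody groups:

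- r = 5%: 0.025/(0.025 + 0.665) = 3.6%.
- True RR 1.0: both groups read 3.6%, so the observed RR is 1.0.
- True RR 0.50: positives 0.0125/(0.0125 + 0.6825) = 1.8%; 0.0180/0.0362 ≈ 0.50.

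Absolute risk is understated, but the ratio is essentially unchanged.

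**4. Non-response that also differs by antibody status.** True RR 1.0, r = 5%.

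- Positives, infected/uninfected response 50%/60%: 0.025/(0.025 + 0.570) = 0.0420.
- Negatives, 70%/60%: 0.035/(0.035 + 0.570) = 0.0579.

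Observed RR is 0.73.

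**5. How far non-response could reach.** Suppose 5% of responders in each group report infection (observed RR 1.0) and follow-up response is 80%. If non-responders have between half and double the responders' risk, group risk runs from 0.80 × 0.05 + 0.20 × 0.025 = 0.045 to 0.80 × 0.05 + 0.20 × 0.10 = 0.060, so the RR lies between 0.75 and 1.33. At 60% response the same rule gives 0.57 to 1.75.

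**The case against.** The study calls itself a pilot, and section 6 describes the analysis as largely descriptive. Self-report is a limited but usable source, and someone ill at month 3 who recovers can report it at month 6 or 12. That stands. A reader might infer that the design cannot say anything about protection, but the Protocol supports only the weaker statement that bias can mimic or hide it.

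Other stronger readings also go too far:

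- *Staff who leave the Trust are lost.* Follow-up goes to the mobile number the participant supplied, or by an alternative method, and nothing ties it to continued employment.
- *Consent covers only data about the antibody test.* Sections 7.1 and 7.2 also mention HR data. Because those data are undefined and section 5 describes details given at testing, later records are not clearly covered, but they are not plainly excluded either.
- *Illness-related non-response by itself distorts the comparison.* Step 3 shows that it does not do so materially.
- *Participants know their result as a matter of record.* This is an inference, and the reporting argument depends on it; the non-response argument does not.
- *Trust records should replace self-report and follow-up should end at the leaving date.* Test results and coded absence depend on the same decision to seek a test, miss testing elsewhere, and would drop leavers whom an SMS could reach. That is a trade-off, not a clear gain.

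It might also be said that this belongs in a statistical analysis plan. Such a plan can add sensitivity analyses for missing answers, but it cannot supply outcome data that were never scheduled for collection or clearly consented to.

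**Conclusion.** The point holds in this form: objective 3, which feeds a measure listed as primary, has a single self-reported outcome source, one reminder against non-response, and no record linkage after baseline. Under the assumed reporting rates, a true RR of 1.0 could be read as 0.48 to 0.80; under other assumed rates, a true RR of 0.50 could be read as 0.95. Non-response biases the RR materially only where response differs by antibody status as well as by illness (0.73 in the example). These figures rest on assumed incidence, reporting and response, and they show scale rather than predict a result. Antibody prevalence and the baseline associations (objectives 1 and 2) are unaffected. This is a worthwhile improvement to make before recruitment, because consent is harder to widen afterwards.

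**What to change.** 1. In the Study Schedule, add Trust-record linkage at 6 and 12 months.
2. State in the online consent and information sheet that consent covers Trust-held SARS-CoV-2 RT-PCR results, COVID-coded sickness absence, and leaving and death dates for 12 months after the antibody test. Bring the descriptions of consent in sections 3, 7.1 and 7.2 into line.
3. Report objective 3 by self-report and by record-confirmed illness side by side, and report follow-up response by baseline antibody status.
4. Keep following leavers by SMS.

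**Cost.** Consent and information-sheet wording, and two further data pulls. The Trust is sponsor and holds the HR data (sections 7.5 and 7.1), and section 7.3 already keeps mobile and employment numbers for linkage. Records miss illness tested outside the Trust and still depend on who seeks a test, so they reduce non-response and recall bias but do not remove differential testing.
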